### Recruitment and Randomization

All participants with eligible AO will be recruited from the 4 hospitals and the community. Recruitment methods mainly include posters, public notice boards, and WeChat public numbers in hospitals and communities. The randomization sequence will be generated by the Clinical Research Center of Yunnan University of Chinese Medicine using a computerized random number generator and placed in opaque envelopes. Stratified randomization will be performed for the 4 clinical centers. To ensure allocation concealment, randomization will be performed by an independent researcher. The research assistant will open the envelope when the participant begins treatment to determine the assigned group and will not disclose grouping information under any circumstances. The acupuncture therapist will be responsible for manipulation only.

### Blinding and Informed Consent

Participants will be informed that they have a 1 in 2 chance of being assigned to 1 of 2 treatments: catgut embedding at acupoints or nonacupoints. The procedure and stimulation of the catgut embedding at acupoints are identical to catgut embedding at nonacupoints. Therefore, participants will be blinded to their treatment assignment. Both groups of participants will be assigned to different treatment rooms to prevent intercommunication. In addition, the acupuncturist, outcome assessor, and those involved in data collection and statistics will be blinded to treatment assignment throughout the trial. Research assistants with knowledge of grouping information will be asked not to communicate with participants or outcome assessors regarding treatment procedures and responses. All patients will be fully informed about the study (including the purpose of the trial and possible risks, etc) prior to participation in the trial, and they have the right to withdraw from the trial at any time without giving a reason. They will sign a written informed consent for voluntary participation prior to enrollment.

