### ACE Group

The selection of acupoints for treatment in the ACE group will be based on the theory that obesity is closely related to the spleen, stomach, and large intestine in traditional Chinese medicine and the Shu-Mu acupoints allocation method commonly used in the current clinical treatment of obesity. The acupoint prescription includes BL20 (Pishu), BL21 (Weishu), BL25 (Dachangshu), RN12 (Zhongwan), ST25 (Tianshu), and LR13 (Zhangmen). All acupoints except Zhongwan are selected bilaterally, for a total of 11 acupoints. The locations of these acupoints are shown in Table 2 and Figure 2.

**Table 2 table2:** The locations of acupoints.

Acupoints	Location
BL20 (Pishu)	In the upper back region, at the same level as the inferior border of the spinous process of the 11th thoracic vertebra (T11), 1.5 B-cun lateral to the posterior median line
BL21 (Weishu)	In the upper back region, at the same level as the inferior border of the spinous process of the 12th thoracic vertebra (T12), 1.5 B-cun lateral to the posterior median line
BL25 (Dachangshu)	In the lumbar region, at the same level as the inferior border of the spinous process of the fourth lumbar vertebra (L4), 1.5 B-cun lateral to the posterior median line
CV12 (Zhongwan)	On the upper abdomen, 4 B-cun superior to the center of the umbilicus, on the anterior median line
ST25 (Tianshu)	On the upper abdomen, 2 B-cun lateral to the center of the umbilicus
LR13 (Zhangmen)	On the lateral abdomen, inferior to the free extremity of the 11th rib

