### Control Group

The acupoints in the control group will be selected based on the acupoints in the ACE group by moving each acupoint 2-3 cm outward horizontally in the median line (CV12 to the left side only) as a nonacupoints (not located on or overlapping with other meridians). They are labeled NA1, NA2, NA3, NA4, NA5, and NA6, respectively, for a total of 11 acupoints. The locations of these acupoints are shown in Table 3 and Figure 2, marked as red points.

**Table 3 table3:** The location of nonacupoints (NAs).

Nonacupoint	Location
NA1	The sitting position of the patient, in alignment with BL20 and the midpoint of the first and second lateral line of the bladder channel
NA2	The sitting position of the patient, in alignment with BL21 and the midpoint of the first and second lateral line of the bladder channel
NA3	The sitting position of the patient, in alignment with BL25 and the midpoint of the first and second lateral line of the bladder channel
NA4	The supine position of the patient, in alignment with RN12 and the midpoint of the left kidney and stomach channel
NA5	The supine position of the patient, in alignment with ST25 and the midpoint of the stomach and spleen channel
NA6	The sitting position of the patient, in alignment with LR13; a vertical line is made from Zhangmen to the spleen channel and the midpoint of the vertical line

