### Manipulation

The specific manipulation is as follows: participants are instructed to be placed in an appropriate position; the separate research assistant marks the acupoints or nonacupoints and routinely disinfects the skin around them; and a sterile sheet is spread, leaving only the buried area. Then, acupuncturists, who are unaware of the group allocation, take a sterile protein cord 1-2 cm long (the length depends on the location of the acupoints), place it on the front end of the trocar, connect the needle core, lift the partial skin with the thumb and forefinger of one hand, and pierce the needle with the other hand. When the piercing reaches the desired depth, apply appropriate push-and-twist techniques, push the needle core and remove the needle tube, and implant the sterile protein string in the subcutaneous tissue or muscle layer of the acupoints. After removing the needle, press the needle hole with a dry cotton ball for half a minute to stop the bleeding. Meanwhile, check that there is no thread residue exposure and no bleeding and then paste a bandage to protect the needle hole. It will be recommended that patients do not take a bath for 24 hours and keep the embedding place dry.

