### Strengths and Limitations

First, this study is a multicenter RCT designed to investigate the efficacy and safety of ACE in AO with a relatively long study period, and the results will provide powerful evidence for the clinical application of ACE in the treatment of obesity. Second, participants’ diet and exercise will not be intervened, which will allow participants to maintain their original lifestyle habits throughout and maximize the efficacy of ACE. Finally, to maintain the success of the double-blind method, contact between participants from different groups will be avoided. The acupuncturist, data evaluator, and statistician will also be hidden from the group assignment, which will minimize possible bias in the results.

Limitations of this study are as follows. First, the relatively short follow-up period of this study may not be comprehensive enough to assess the durability of ACE efficacy. Second, the selection of nonacupuncture acupoints as an intervention in the control group in this study may inevitably produce some efficacy as well [62,63]. Third, only patients with AO are selected as the study population in this study, and further studies on different types of obesity will be conducted at a later stage.

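### The acupuncturist is stated to be blinded, but the two point sets differ at the midline, so the operator can tell which arm is being treated

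*Protocol article*

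**What the plan says.** Operator blinding is claimed in three places in the protocol article.

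- Blinding and Informed Consent: "the acupuncturist, outcome assessor, and those involved in data collection and statistics will be blinded to treatment assignment throughout the trial".
- Manipulation: "acupuncturists, who are unaware of the group allocation, take a sterile protein cord 1-2 cm long".
- Strengths and Limitations, where it is offered as a protection against bias: "The acupuncturist, data evaluator, and statistician will also be hidden from the group assignment".

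The ACE Group section lists five bilateral acupoints plus CV12. Table 2 places CV12 as follows: "On the upper abdomen, 4 B-cun superior to the center of the umbilicus, on the anterior median line". The Control Group section derives the nonacupoints by moving each acupoint 2-3 cm outward, with "CV12 to the left side only". Table 3 accordingly puts NA4 between the left kidney and stomach channels.

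On rooms, Blinding and Informed Consent says: "Both groups of participants will be assigned to different treatment rooms to prevent intercommunication".

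**The concern.** The person who inserts the needle has to look at the insertion sites. If their layout differs visibly between the arms, keeping the allocation from the operator by other means does not blind the operator.

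The operator meets each participant at six sessions and, under Manipulation, uses judgement about depth and needle technique. An operator who knows the arm could, without intending to, treat or encourage the two groups differently. Appetite is self-rated and is the outcome most open to this. Waist circumference could be affected only indirectly, for example if encouragement changed eating or activity, which the trial leaves uncontrolled.

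The trial report is also at stake. If it repeats the present wording, it will claim a protection that the design does not provide.

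**Working it through.** No arithmetic decides this point, and the document gives no figure to reproduce. The check sets the blinding statements beside the point sets.

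**Inputs**

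- ACE set: five bilateral points and one midline point (ACE Group, Table 2).
- Control set: the same points displaced 2-3 cm outward, with the midline point moved left (Control Group, Table 3).
- Sessions: 6, two weeks apart (Interventions).
- Operator: a nationally qualified acupuncturist (Interventions).
- Masking steps: a separate research assistant marks and disinfects the sites, and a sterile sheet leaves the embedding area exposed (Manipulation). The therapist's role is limited to manipulation (Recruitment and Randomization).

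**Step 1. Count the sites.** ACE: 5 × 2 + 1 = 11. Control: 5 × 2 + 1 = 11. The number of insertions does not distinguish the arms.

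**Step 2. Compare positions.**

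| | ACE | Control |
|---|---|---|
| Paired sites | 10, at the acupoints | 10, displaced outward |
| Midline abdominal sites | 1 (CV12) | 0 |
| Unpaired sites off the midline | 0 | 1 (NA4, left) |

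**Step 3. Carry this over the course.** Assuming that the full set is used at each session, an ACE participant receives 6 × 1 = 6 midline insertions and a control participant 6 × 0 = 0. The cue is present at every session.

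**Step 4. Ask whether the operator would recognise it.** Midline or not midline is a simple visual distinction. The ACE Group section also describes the acupoint prescription as one in common clinical use for obesity, so a qualified acupuncturist is likely to know it.

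**Step 5. Ask whether the masking steps remove the cue.** Marking by an assistant means that the operator neither chooses the sites nor has to be told the arm. The sheet covers the surrounding skin. Neither step conceals where the mark is from the person inserting at it. The statement that procedure and stimulation are identical is used in the document to support participant blinding and does not concern site position.

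**Step 6. Rooms.** The stated purpose is to keep participants of the two groups apart. The document does not say whether a room is fixed to an arm or whether one operator serves both. If rooms are fixed by arm and the operator works in both, the room is a second cue. The conclusion from Steps 1 to 5 does not need it.

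**The case against.** The strongest reply is that real safeguards exist: independent marking, draping, a therapist confined to manipulation, and informed assistants told not to discuss treatment with participants or assessors. These stand as measures against deliberate disclosure and against the operator selecting sites. They do not answer the midline difference.

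A reader might infer three stronger points, and the document supports none of them.

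- *Double-blinding fails as a whole.* The evidence concerns the operator only. Participants receive the same procedure in both arms, and outcomes are measured by a separate researcher. A trial that blinds participants and assessors can still reasonably be called double-blind, so the title need not change on this ground.
- *The rooms reveal the arm to assessors and participants.* Only treatment rooms are separated. Nothing says that measurements are taken there or that assessors know which room was used. A participant who is not told what a room stands for learns nothing from it.
- *The operator may freely vary the implanted length between 1 and 2 cm.* The text says that "the length depends on the location of the acupoints". Length is thus tied to body site, and the control sites correspond one for one to the acupoints. The range is not a measure of operator discretion.

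It is also fair to say that waist circumference is a tape measurement under a defined procedure, so an operator effect on it would have to act through the participant. A test of blinding success may be left to a fuller document, and its absence here is not an error.

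**Conclusion.** The point holds for the operator. The article three times states a design property, acupuncturist blinding, that its own point sets make untenable. The supported description is participant- and assessor-blinded, with the operator not reliably blinded.

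This rests on two assumptions: that the operator sees the marks at which the needle goes in, which the procedure requires, and that the point sets are used as tabulated. The room cue is conditional on rooms being fixed by arm.

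The size of any resulting bias cannot be computed from the document. It is most plausible for self-rated appetite, a secondary outcome, and indirect for waist circumference, the primary outcome. The correction should be made, but the point does not invalidate the primary comparison.

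**What to change.** 1. In Blinding and Informed Consent, Manipulation, and Strengths and Limitations, remove the acupuncturist from those said to be blinded. Describe the trial as participant- and assessor-blinded with the operator not reliably blinded, and stop citing operator blinding as protection against bias.
2. Do not tie treatment rooms to arms. Prevent contact by scheduling participants individually, so that neither room nor appointment slot reveals the allocation. Giving each arm its own slots would only replace one code with another.
3. Optionally, record participants' and assessors' guesses of allocation at the existing week-12 visit and report them beside the waist circumference and appetite results.

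The cost is a less favourable blinding label, minor scheduling work and, if the third item is adopted, one question per person at a visit already planned. The article was published in July 2023 and expects recruitment to end in September 2023. Items 2 and 3 can therefore reach only participants still in the trial, while the wording can be corrected whatever the stage.

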### Sample Size Calculation

According to the existing literature [45], the mean BMI of simple obesity was 32.30 kg/m^2^, whereas after 12 weeks and 6 treatment of acupuncture combined with a low-energy diet, the mean BMI was 30.98 kg/m^2^, and the improvement value was 1.32 kg/m^2^. In contrast, the improvement value was 1.02 kg/m^2^ in a control group with a variation from 32.74 kg/m^2^ to 31.73 kg/m^2^ when treated by sham acupuncture combined with a low-energy diet, and the SD of the 2 groups was 0.31 kg/m^2^. In this project, the expected improvement value of the mean BMI of the Shu-Mu acupoints embedding group after treatment is 1.14 kg/m^2^ and that of the nonacupoints embedding group is 0.9 kg/m^2^, with the SD of each group being 0.31 kg/m^2^. The significant level is ɑ=.05, and the power of a test is 1 – β = 0.95. The sample size is 84 as calculated by German G*power software 3.1 [46]. According to the 10% dropout, the total sample is 92 cases, and 46 cases will be assigned to each group.

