### Statistical Analysis

All data will be analyzed by SPSS statistical software (version 19.0; IBM Corp). The clinical outcomes and baseline characteristics are based on the intention-to-treat population, which will include participants who have received at least one treatment. Continuous variables will be shown as the mean and SD, whereas the nonnormally distributed variables will be presented as the median and IQR. Categorical variables will be described as numbers and percentages. The normality of continuous variables will be determined using the Shapiro-Wilk test, Kolmogorov-Smirnov test, skewness, and kurtosis. The homogeneity of continuous variables will be determined by *F*-test, Brown-Forsythe, and Bartlett tests. Comparisons between groups will be made using independent samples 2-tailed *t* tests or nonparametric tests (Mann-Whitney *U* test). Repeated measures within groups (≥3) will be analyzed using one-way ANOVA or nonparametric (Friedman) tests. Paired 2-tailed *t* tests or nonparametric tests (Wilcoxon test) will be used for within-group pre-post comparisons. For categorical data, the chi-square test will be used to assess the significance of differences. Values of *P*<.05 will be considered significant using a 2-sided test.

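### The sample size of 84 cannot be reproduced from the printed BMI inputs, which need 90 for 95% power, and the dropout step to 92 falls slightly short

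*Protocol article*

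**What the plan says.** The section Sample Size Calculation bases the calculation on change in BMI. For the active arm, "the expected improvement value of the mean BMI of the Shu-Mu acupoints embedding group after treatment is 1.14" kg/m²; for the control arm, "that of the nonacupoints embedding group is 0.9" kg/m², "with the SD of each group being 0.31" kg/m². The error rates are given as "The significant level is ɑ=.05" and "the power of a test is 1 – β = 0.95". The result is "The sample size is 84 as calculated by German G*power software 3.1". The allowance for loss follows: "According to the 10% dropout, the total sample is 92 cases, and 46 cases will be assigned to each group".

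That section does not give the sidedness, the test or the standardised effect entered in the software. Statistical Analysis supplies two of the three: groups are compared by independent-samples t test, with Mann-Whitney as the non-parametric alternative, and P values below .05 "will be considered significant using a 2-sided test". Study Design and Setting gives 1:1 allocation.

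**The concern.** The article prints every input that a two-sample calculation needs, names the software and prints the answer, so a reader can repeat the calculation. The answer does not come back. The dropout step is a separate slip in the same direction: it inflates by a multiplier where a divisor is needed.

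At stake is the accuracy of two figures that the final report will repeat, the required sample size and the power. The number to be recruited is not in question.

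**Working it through.** **Inputs**
- Difference in mean BMI improvement: 1.14 − 0.90 = 0.24 kg/m² (Sample Size Calculation)
- SD per group: 0.31 kg/m² (same section)
- Alpha 0.05 and power 0.95 (same section); two-sided (Statistical Analysis)
- Allocation 1:1 (Study Design and Setting)
- Dropout 10% (Sample Size Calculation)

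Standardised effect: d = 0.24 / 0.31 = 0.774.

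**Step 1. Try to reproduce 84**

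Normal approximation, per group: n = 2 × (1.960 + 1.645)² / d² = 2 × 12.995 / 0.5994 = 43.4, rounded up to 44, so 88 in total.

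Exact t test: power = P(|T| > t crit), where T is noncentral t with 2n − 2 degrees of freedom and noncentrality d × √(n/2).

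| Per group | Total | Noncentrality | t crit | Power |
|---|---|---|---|---|
| 42 | 84 | 3.548 | 1.989 | 93.9% |
| 44 | 88 | 3.631 | 1.988 | 94.9% |
| 45 | 90 | 3.672 | 1.987 | 95.3% |

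The smallest equal-arm design that reaches 95% is 45 per group, 90 in total.

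**Step 2. Look for a setting that gives 84**

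| Setting (exact t test) | Total |
|---|---|
| Two-sided, 95%, d = 0.774 | 90 |
| One-sided, 95%, d = 0.774 | 74 |
| Two-sided, 90%, d = 0.774 | 74 |
| Two-sided, 95%, difference 0.30 (the cited trial: 1.32 − 1.02), SD 0.31 | 58 |
| Two-sided, 95%, d = 0.77 | 90 |
| Two-sided, 95%, d = 0.78 | 88 |
| Two-sided, 95%, d = 0.80 | 84 |

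Of these settings, only d = 0.80 returns 84. It would arise from rounding 0.774 up to one decimal, or from an SD of 0.30 in place of 0.31 (0.24 / 0.30 = 0.80). The article gives neither.

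**Step 3. The dropout step**
- As apparently done: 84 × 1.1 = 92.4, taken as 92.
- To keep 84 after a 10% loss: 84 / 0.9 = 93.3, so 94 in equal arms.
- What 92 leaves: 92 × 0.9 = 82.8, about 83.
- Starting from 90: 90 / 0.9 = 100.

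**Step 4. Power for BMI with 92 enrolled, on the printed inputs**

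| Analysed | Power |
|---|---|
| 82 (41 + 41) | 93.4% |
| 83 (42 + 41) | 93.6% |
| 84 (42 + 42) | 93.9% |
| 92 (46 + 46) | 95.7% |

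**The case against.** Three points on the other side have force.

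*The effect on power is small.* The loss is 95 − 93.6 = 1.4 to 95 − 93.4 = 1.6 percentage points after the planned dropout. With no loss of data, power is 95.7%, above target. The intention-to-treat set includes everyone who received at least one treatment, and envelopes are opened as treatment begins, so nearly everyone randomised should belong to it. This stands, with one limit: belonging to the set does not supply a missing measurement, and the sample size section itself plans for a 10% loss. A reader might infer that the trial is underpowered or that 95% is out of reach. The documents do not support that.

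*Rounding may explain 84.* The control improvement is printed to one decimal. The section shows rounding elsewhere: a fall from 32.74 to 31.73 is 1.01, but is given as 1.02. An unrounded difference of 0.248 with SD 0.31 gives d = 0.80 and hence 84. This is possible but cannot be confirmed. It limits the finding to the figures as printed. It does not make 84 follow from them, nor does it show that d = 0.80 was in fact entered.

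*The dropout shortcut is common and costs two participants* (94 against 92). That is true, and alone it would hardly merit a comment. It belongs here because the same sentences need correcting.

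A reader might also infer that the Mann-Whitney option widens the gap, because its efficiency relative to the t test is 0.955. That efficiency holds for normal data, for which the plan would use the t test. For other distributions it can be lower or higher: with a logistic distribution the requirement is 82, below 84. No general shortfall follows.

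**Conclusion.** The point holds as an error in the stated figures, with little effect on power. On the printed inputs, 95% power needs 90 evaluable participants by exact t test (88 by normal approximation), so 84 is 6 short (or 4). With the 10% dropout allowance, 90 evaluable means 100 enrolled, 8 more than the 92 planned. Power for BMI with 92 enrolled lies between about 93.4% (10% lost) and 95.7% (none lost).

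These figures assume that the printed difference and SD are exact, that the test is the two-sided t test of Statistical Analysis, and that losses are about equal between arms.

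All of them concern BMI. The primary outcome is waist circumference, for which the sample size section gives no effect size or SD. Neither the stated 95% nor the corrected 93 to 96% should be read as the trial's power for its primary outcome.

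**What to change.** Keep 92 enrolled and correct the text of Sample Size Calculation:

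1. State the standardised effect, the test and the sidedness entered in the software. If unrounded inputs were used, print them.
2. Unless those inputs do give 84, replace 84 and 0.95 with this: for a BMI difference of 0.24 kg/m² and SD 0.31 kg/m² (d = 0.774), two-sided alpha 0.05, 95% power would need 90 evaluable participants, or 100 enrolled with 10% dropout; 92 enrolled gives about 93% power with 10% dropout and about 96% with none.
3. Calculate the dropout allowance as N / (1 − 0.10).
4. Say that these figures are for BMI, a secondary outcome, and do not establish power for waist circumference.

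The cost is a few sentences and a slightly less favourable stated power. Recruitment, conduct and analysis do not change.
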